### Implementation and dissemination: Activities

The intervention will be implemented from September to February 2017/18 and 2018/19 (Fig. 1). The intervention will be adapted based upon the evaluation results of the first wave.

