*Population-based registry study on bloodstream infections in Thuringia.*
*Hypothesis.* The incidence of pneumococcal bacteraemia among patients aged ≥60 years in Thuringia will not increase further or will be reduced during the intervention period compared with the baseline measurement before intervention.*Study population.* To further explore the burden of IPD in Thuringia, we include all in- and outpatients aged ≥60 years regardless of their vaccination status with at least a single positive blood culture for *Streptococcus pneumoniae* registered by ALERTSNet between 1 October, 2014 and 1 October, 2019. ALERTSNet is a prospective population-based registry for bloodstream infections in Thuringia. ALERTSNet was initiated by funding from the Federal Ministry of Health and land resources in 2013, and aims to cover the whole of Thuringia by 2018 Therefore, no power calculations were performed as ALERTSNet aims to involve a complete survey of a whole federal state and not a sampling survey. All data obtained by ALERTSNet are anonymous. Data by ALERTSNet are equally protected from the access by unauthorized persons as computer systems processing personal data in the healthcare sector. Security measures include that computer systems are physically protected from unauthorized access and inlet and outlet communication connections are protected by encryption according to current industrial standards.*Outcome measures.* We identify proven cases of pneumococcal bacteraemia and associated patient data concerning age, sex and date of positive blood culture in all patients aged ≥60 years recorded by ALERTSNet since 1 October, 2014. As ALERTSNet currently does not cover all Thuringia (13.6% of Thuringia in 2014, 32.6% of Thuringia in 2015, and 50.8% of Thuringia in 2016), the increasing catchment areas have to be considered and incidence rates have to be extrapolated during the study period.*Statistical analyses.* Mean changes in the incidence and demographic data of patients with pneumococcal bacteraemia will be compared in the period prior to and during the intervention in Thuringia (1/10/2014–30/09/2017 versus 1/10/2017–30/09/2019). As there is no other population-based registry for bloodstream infections in Germany, no direct comparison to another federal state is possible. Although missing data might be possible for demographic data, they are not expected for the main outcome incidence (defined by the number of cases and date of positive blood culture for *S. pneumoniae*). Therefore, all patients reported by ALERTSNet ≥60 years with pneumococcal bacteraemia will be included in the analysis. Currently, retrospective analysis of proven cases of pneumococcal bacteraemia in Thuringia by ALERTSNet from 1 October 2014 to 30 September 2016 is completed and first prospective data for the period of 1 October 2016 to 30 September 2017 are available.

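### The bacteraemia hypothesis that incidence will not rise further is paired with a before/during comparison that has no trend term, so a halted rise can appear as an increase

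*Protocol article*

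**What the plan says.** The point concerns component b of the secondary outcomes in the Protocol article, the registry study on bloodstream infections in Thuringia. Its hypothesis is: "The incidence of pneumococcal bacteraemia among patients aged ≥60 years in Thuringia will not increase further or will be reduced during the intervention period". The sentence goes on to name the reference, so that in full the claim is that incidence "will not increase further or will be reduced during the intervention period compared with the baseline measurement before intervention".

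The analysis is given as: "Mean changes in the incidence and demographic data of patients with pneumococcal bacteraemia will be compared in the period prior to and during the intervention", with the periods set at "1/10/2014–30/09/2017 versus 1/10/2017–30/09/2019". That is three years against two. No slope, trend or projection is mentioned.

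The paragraph also explains why there is no concurrent comparator: "As there is no other population-based registry for bloodstream infections in Germany, no direct comparison to another federal state is possible". It gives the registry's coverage as "13.6% of Thuringia in 2014, 32.6% of Thuringia in 2015, and 50.8% of Thuringia in 2016" and says that incidence will have to be extrapolated to allow for the growing catchment.

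The neighbouring components are worded differently. The hospital discharge study (component a) and the community-acquired pneumonia study (component c) both compare trends over 2014–2019, against the other federal states and against the whole of Germany respectively.

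**The concern.** A claim that incidence will not rise *further* is a claim about a slope: incidence was climbing, and the climb stops. A comparison of two period averages does not address a slope. When incidence climbs through the prior period, the average of that period lies below the level reached at its end. If the climb then stops, the intervention-period average sits at the end level and is higher than the prior average. The estimate shows an increase although the first limb of the hypothesis is true.

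The error also runs the other way. If incidence was already falling, the comparison attributes the continuing fall to the campaign.

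Components a and c have a control region that could absorb a background trend. Component b has none, so its own pre-campaign course is the only counterfactual available, and the stated analysis does not use it. It is also the only component whose cases are defined by a positive blood culture.

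**Working it through.** **Inputs.** From the article: prior period 1 October 2014 to 30 September 2017; intervention period 1 October 2017 to 30 September 2019; coverage 13.6%, 32.6% and 50.8% in 2014, 2015 and 2016. The article gives no incidence, growth rate or sample size for this component, so there is no figure of its own to reproduce. The growth rate *g* is an assumption, shown at 5%, 10% and 20% a year.

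**Check 1: yearly levels.** Set the last pre-campaign year to 1. The two earlier years are then 1/(1+g) and 1/(1+g)². Suppose incidence stays at 1 throughout the intervention period.

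- Equal weights: prior mean = [1 + 1/(1+g) + 1/(1+g)²] / 3.
- Coverage weights: prior mean = [50.8 + 32.6/(1+g) + 13.6/(1+g)²] / 97.0. This treats the prior rate as pooled over covered population and assigns the three calendar-year coverages to the three registry years. That is an approximation, because the registry years start in October and no 2017 coverage is given.
- Apparent change after a plateau = 1/(prior mean) − 1. After a true 5% fall from the last pre-campaign year it is 0.95/(prior mean) − 1.

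| g (assumed) | Prior mean, equal weights | Plateau | True 5% fall | Prior mean, coverage weights | Plateau | True 5% fall |
|---|---|---|---|---|---|---|
| 5% | 0.953 | +4.9% | −0.3% | 0.971 | +3.0% | −2.2% |
| 10% | 0.912 | +9.7% | +4.2% | 0.945 | +5.8% | +0.5% |
| 20% | 0.843 | +18.7% | +12.7% | 0.901 | +11.0% | +5.4% |

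**Check 2: continuous linear rise.** Let incidence be I₀ at the start and rise by g each year, stopping on 1 October 2017.

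- Prior mean = I₀ + 1.5g. Plateau = I₀ + 3g. Difference = +1.5g.
- With g at 5% of I₀: 115/107.5 − 1 = +7.0%. With g at 10%: 130/115 − 1 = +13.0%.
- These exceed the figures in check 1 because the plateau is now the level at the very end of the prior period, not the average of its last year.
- The campaign starts in September 2017, a month before the cut. A plateau from 1 September gives +6.6% and +12.3%.
- If the rise simply continued, the intervention mean would be I₀ + 4g and the difference +2.5g. A complete halt therefore still shows 1.5/2.5 = 60% of the increase expected with no effect at all.

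**Check 3: falling baseline, no campaign effect.** With a steady linear fall of g a year, the prior mean is I₀ − 1.5g and the intervention mean I₀ − 4g. At 5% of I₀ this is 80/92.5 − 1 = −13.5%, all of it from the existing trend.

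**Check 4: the other reading.** If *mean changes* means the average yearly change within each period, a rise followed by a plateau gives +g before and 0 during, which supports the hypothesis. The two readings give opposite answers from the same data.

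**Check 5: against the trend.** For the linear plateau, the slope changes by −g and the intervention mean lies (I₀ + 4g) − (I₀ + 3g) = 1.0g below the projection. That is the sign the hypothesis predicts.

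**The case against.** The strongest reply is that the hypothesis names its own reference, the baseline measurement before intervention. On that reading a baseline-against-intervention comparison is what was promised, and *further* is only loose wording. This partly stands. But the sentence then carries two references, the course of incidence and its baseline level, and under a rising baseline they conflict. One of them has to give way.

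The second reply is that *mean changes* may mean change within each period. That cannot be excluded. The sentence sets one period against the other, and components a and c say trends where trends are meant, so period means is the more natural reading. If the other was intended, the estimand needs stating.

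The third is that model details belong in an analysis plan that is not shown. That holds for the choice of model. It does not cover the contrast, which the article itself fixes together with its dates.

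Several stronger readings are tempting and should not be drawn:

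- *The plan would reject a true hypothesis, or declare the campaign a failure.* The article states no test, alpha level or decision rule for this component. It is one of five sources meant to cross-validate each other, and invasive pneumococcal disease is also studied in the discharge data against other states.
- *Incidence was rising.* The word *further* implies it, but no figure shows it. The Background's remark about increasing rates concerns severe manifestations such as sepsis.
- *Any modest reversal would be hidden.* At 5% growth a 5% fall does not appear as an increase under either weighting.
- *Sepsis education would raise blood-culture taking and so inflate counts.* Nothing in the article bears on culture frequency.

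The missing control region is disclosed with its reason. It is a constraint, not an error.

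**Conclusion.** The mismatch between hypothesis and stated analysis is real, and should be corrected in a secondary component. Read as period means, with a steadily rising baseline, a halt in the rise shows as an increase in every variant checked; the sign is algebra and only the size is assumed. On yearly levels it is about +3% to +5% at 5% growth a year and about +6% to +10% at 10%, depending on whether pre-campaign years are weighted by coverage. It is larger if the rise runs right up to the cut. A prior decline biases in the campaign's favour.

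The conclusion depends on two things the article does not settle: the direction of the pre-campaign trend and the meaning of *mean changes*. With a flat baseline there is no bias. The sponsor can check the first point directly, since the article says the data from October 2014 to September 2016 have been analysed and first data for 2016–2017 are available.

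**What to change.** State the estimand as change relative to the pre-campaign trend. Fit a Poisson model, or one allowing overdispersion, to monthly or quarterly counts with a catchment-population offset, a pre-campaign slope, and a change in level and slope at 1 October 2017. Report the observed rate beside the rate projected from 2014–2017. Keep the simple period comparison as descriptive.

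The minimal alternative is to leave the analysis alone, say that it compares period means, and reword the hypothesis to mean incidence not higher than the pre-period mean.

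Running the same model on bloodstream infections from organisms outside the vaccine's target is an optional internal control. It depends on the registry supplying those data, which the article does not list for this study.

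The cost is wording and modest programming; culture dates are already collected, and the article describes evaluations from sources other than the surveys as still pending. The price is a wider interval than a comparison of means, and a pre-campaign slope that must be estimated while coverage grows from 13.6% to 50.8% over 2014–2016. Centre entry could pass for a trend, so repeat the slope estimate in centres covered throughout.

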##### Overall hypothesis

If the primary outcome with increase in vaccination rates in Thuringia is reached in the elderly, we also expect a reduction in the incidence of influenza, pneumococcal pneumonia, invasive pneumococcal disease (IPD) and to a lesser extent sepsis and pneumonia in the target population also.
*Retrospective nationwide hospital discharge database study.*

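### The bacteraemia registry hypothesis accepts an unchanged incidence as support, in a before/after comparison within Thuringia from which no campaign effect can be inferred

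*Protocol article*

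**What the plan says.** All of this is in the protocol article, under the secondary outcomes.

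- **Overall hypothesis.** If vaccination rates rise, "we also expect a reduction in the incidence of influenza, pneumococcal pneumonia, invasive pneumococcal disease (IPD") among other conditions. The expected direction is a fall.
- **Item b, registry study, hypothesis.** Pneumococcal bacteraemia at age 60 and over "will not increase further or will be reduced during the intervention period compared with the baseline measurement before intervention".
- **Item b, analysis.** Mean changes in incidence are compared between two periods in Thuringia, "1/10/2014–30/09/2017 versus 1/10/2017–30/09/2019". No margin, test or trend model is given.
- **Item b, comparator.** "As there is no other population-based registry for bloodstream infections in Germany, no direct comparison to another federal state is possible".
- **Item b, scope and cases.** "ALERTSNet is a prospective population-based registry for bloodstream infections in Thuringia", and this study takes from it patients "with at least a single positive blood culture for *Streptococcus pneumoniae* registered by ALERTSNet".
- **Item b, coverage.** "13.6% of Thuringia in 2014, 32.6% of Thuringia in 2015, and 50.8% of Thuringia in 2016"; the registry "aims to cover the whole of Thuringia by 2018". The article says incidence must be extrapolated to allow for this growth.

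The other regional comparisons are concurrent: item a (hospital discharge data) against the other federal states, item c (pneumonia quality-assurance data) against all of Germany, and item e (physician claims data) against areas outside Thuringia. The five sources are meant to validate one another.

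**The concern.** A flat rate is what a campaign with no effect produces when the background is stable, yet the registry hypothesis lists it as a confirming result. In items a and c, a flat rate shared by both regions would confirm nothing, because the prediction is relative to a concurrent population. In item b the only yardstick is Thuringia's own earlier years, so any shift in season, blood-culture practice, reporting sites or underlying trend enters the result undiluted.

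The reason given for having no comparator rules out a second federal state. It does not rule out a control series inside a registry that is described as covering bloodstream infections generally.

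At stake is whether a null result from this source is reported as agreeing with the others.

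**Working it through.** **Nothing to reproduce.** The article gives no incidence, case count, test or power for this outcome. The check is therefore how often a campaign with no effect would meet the stated prediction.

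**Inputs from the article.** 500,000 residents aged 60 and over; coverage 13.6%, 32.6% and 50.8%; three years before against two years during.

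**Assumptions.**
- The three calendar-year coverage figures are applied to the three baseline years, which run October to September.
- Coverage in the two intervention years is 75% then 100%, or 50.8% in both.
- Incidence is 5, 10, 20 or 40 per 100,000 per year in the first year.
- The background trend is −5%, 0, +5% or +10% per year.

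**Person-years.** Before: 500,000 × (0.136 + 0.326 + 0.508) = 485,000. During: 500,000 × 1.75 = 875,000, or 500,000 × 1.016 = 508,000. At 10 per 100,000 and no trend, the expected cases are 48.5 before and 87.5 (or 50.8) during.

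**Two readings of the prediction**, computed exactly for two independent Poisson counts:
- *Point estimate:* observed rate during ≤ observed rate before.
- *No significant increase:* conditional binomial test, one-sided 0.025. The article does not state this rule; it is included as the looser reading.

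Probability that a campaign with **no effect** meets the prediction (range over the assumed incidences and coverages):

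| Background trend | Point estimate | No significant increase |
|---|---|---|
| −5% per year | 0.64–0.88 | above 0.99 |
| flat | 0.495–0.507 | 0.977–0.982 |
| +5% per year | 0.10–0.36 | 0.77–0.96 |
| +10% per year | 0.004–0.22 | 0.27–0.90 |

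**A halted rise.** Suppose incidence rises 10% a year through the baseline (1.00, 1.10, 1.21) and then stays at 1.21. The unweighted baseline mean is 3.31 / 3 = 1.103, so the ratio of period means is 1.21 / 1.103 = 1.10. Weighted by coverage, the baseline mean is (0.136 × 1.00 + 0.326 × 1.10 + 0.508 × 1.21) / 0.970 = 1.144, and the ratio is 1.21 / 1.144 = 1.06. Incidence has stopped rising, as the wording predicts, but the planned comparison of period means shows an increase of 6–10%.

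**What a confidence-interval rule changes.** With a flat background, the 95% interval for the rate ratio lies wholly below 1 in about 2.5% of null cases, against about 50% for the point estimate. It does not remove a trend. At 20 per 100,000, a 5% annual fall and 75%/100% coverage, expected cases are 90.4 and 145.8. The rate ratio is (145.8 / 875,000) / (90.4 / 485,000) = 0.89, its log is −0.113, and its standard error is √(1/90.4 + 1/145.8) = 0.134. The chance that the interval lies below 1 is then Φ(−1.96 + 0.113 / 0.134) = Φ(−1.12), about 13%, with no campaign effect. Hence the further control series.

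**The case against.** **The headline probability depends on the background.** A reader might infer that a campaign with no effect meets this hypothesis half the time or more whatever the background. The documents do not support that. The word *further* hints at an earlier rise, and on the point-estimate reading a 5% annual rise brings the figure down to 10–36%. This objection stands.

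**About 50% is a property of any directional point-estimate criterion.** Changing the wording to a reduction, and nothing else, would leave it in place. This stands too, so the remedy has to include the interval rule.

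**The 98% figure rests on a rule the plan does not contain.** Correct. It shows only how loose that reading would be.

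**The study can still disagree.** A reader might infer that the registry study could never contradict the campaign. It can: on the point-estimate reading, a background rise of 5% a year would fail the hypothesis in roughly 64–90% of repetitions. The difficulty is attribution.

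**Conflict with the overall hypothesis is mild.** That hypothesis is conditional on vaccination rates rising, and halting a rise is a sensible single-region prediction. But the planned comparison of period means does not test a halted rise, as the calculation shows.

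**The gap is disclosed and partly covered.** The article gives its reason for having no other-state comparator, item a compares IPD with other states, and the limitations mention the registry's incomplete coverage. This reduces the damage but does not alter what item b counts as support.

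**The control series is inferred.** The article does not say that this study holds records for other pathogens, and parallel trends between pathogens would have to be assumed. The series therefore belongs in a supporting role.

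**Conclusion.** The point holds in a conditional form. The registry hypothesis accepts an unchanged rate in a single-region before/after comparison as support, where the overall hypothesis expects a reduction and the other regional comparisons are concurrent. With a flat background, a campaign with no effect satisfies it about 50% of the time on the point estimate; with a 5% annual fall, 64–88%. With a rising background the figure drops below one half, and a campaign that only stopped the rise could be scored as a failure. In none of these cases can the result be assigned to the campaign.

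The probabilities rest on assumed incidence, trend and coverage after 2016, and on independent Poisson counts. They do not model changes in case mix as the catchment grows. The flat-background figures barely move over the assumed range; those for a trend move a good deal. This is one secondary source among five, so the change is advisable rather than critical.

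**What to change.** 1. State the item b hypothesis as a reduction, in line with the overall hypothesis.
2. Report the before/after rate ratio with a 95% confidence interval on the registry's covered person-years. Claim support only if the interval lies wholly below 1, and label an unchanged rate as no evidence of effect.
3. As a supporting analysis, where the registry can supply the counts, divide this ratio by the corresponding ratio for bloodstream infections with pathogens that neither vaccine targets, at age 60 and over, from the same sites and dates. This removes changes in catchment, blood-culture practice and reporting that both series share. State the parallel-trend assumption.
4. Interpret the result beside the item a contrast of IPD between Thuringia and the other states.

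**Cost.** A change of wording, one extra registry extract, a wider interval for the ratio of ratios, and a stricter claim. The article says evaluations from sources other than the survey are still pending and reports registry data only to 30 September 2017, so the change can be made before the intervention-period results are analysed.

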Due to the multi-methods and multi-data sources approach for intervention evaluation the results will be multifaceted, too. While this creates unique opportunities, it also comes with considerable challenges: data may sometimes be difficult to compare. Furthermore, limitations of the individual data sources are the following:Microbiological diagnostics of the secondary outcome pneumonia is not standardised between German hospitals.Although ALERTSNet aims to cover all of Thuringia, it only covers specific centres at certain times.ICD codes used by the German DRG statistics are considered to have high specificity, but only moderate sensitivity, thus being prone to an underestimation of disease prevalence, e.g., for sepsis by up to 3.5-fold [71, 72].Results from cohort studies assessing the impact of vaccination on disease incidences or resource utilisation might be subject to confounding by indication or healthy vaccinee bias. However, relevant covariates will be collected and adjusted analyses will be performed to mitigate this risk.Awareness for the intervention could be so low that stratifying data per material or source of information might be difficult. If awareness is below 50% in the first 100 participants of the representative study after wave one, participants with awareness for the intervention will be oversampled to reach a sample of at least *n* = 350 participants per group. Otherwise, reliable statistical analyses about the effects of the single aspects of the intervention will be not possible.

The intervention is limited to two seasons and an observation period before and after each launch. Some effects of the intervention may only become apparent after a longer period of time and will thus be missed due to the limited duration of the observation.

In sum, this study will add further knowledge to theory-based and evidence-informed development of interventions based on the assessment of relevant behavioural determinants within the target group. Lessons learned from this project can have an additional positive impact on campaign development especially for the growing 60+ age group for various other health behaviours (e.g., healthy diets, physical activity, age-related prevention campaigns such as screenings). The study uses a sophisticated and multi-faceted approach to evaluation, which can identify chances and pitfalls of several data sources. It could therefore serve as a benchmark for future evaluation studies.

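### The bloodstream-infection registry compares extrapolated incidence before and during the intervention while its catchment grows; extrapolation does not correct for which areas are observed, so area differences could mimic or mask an effect

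*Protocol article*

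**What the plan says.** All of this is in the protocol article, under secondary outcomes, item b (the population-based registry study on bloodstream infections in Thuringia), unless noted.

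- **Coverage.** The registry covered "13.6% of Thuringia in 2014, 32.6% of Thuringia in 2015, and 50.8% of Thuringia in 2016", and it "aims to cover the whole of Thuringia by 2018". Achieved coverage for 2017 to 2019 is not given.
- **Handling of the growing catchment.** "the increasing catchment areas have to be considered and incidence rates have to be extrapolated during the study period". No method is described beyond this.
- **Contrast.** "Mean changes in the incidence and demographic data of patients with pneumococcal bacteraemia will be compared in the period prior to and during the intervention", the periods being "1/10/2014–30/09/2017 versus 1/10/2017–30/09/2019".
- **Analysis set.** Every reported patient aged 60 or over with pneumococcal bacteraemia is included. The comparison is not restricted to areas observed throughout.
- **Control.** None: "no direct comparison to another federal state is possible".
- **Hypothesis.** Incidence "will not increase further or will be reduced during the intervention period compared with the baseline measurement before intervention".
- **Limitation, in the Discussion.** "Although ALERTSNet aims to cover all of Thuringia, it only covers specific centres at certain times". No remedy follows.

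**The concern.** Multiplying the covered cases up to the whole state treats areas not yet covered as if they had the same incidence, and the same habit of taking blood cultures, as areas already covered. Because the catchment grows across the study, the before-period describes mainly early-joining areas, while the during-period describes a wider set, perhaps the whole state. The two rates then refer to different populations even though both carry the label Thuringia.

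In a design with a concurrent comparison, or one restricted to areas observed throughout, this could be seen or removed. Here there is neither, so any difference between early and late areas passes directly into the before/during contrast. What is at stake is how the registry result on invasive pneumococcal disease is read: a fall could be credited to the campaign, or a real benefit hidden, because of who was in the registry when.

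**Working it through.** The article gives no sample size, event count or effect size for this component, so there is no planned figure to reproduce. The check asks what the planned contrast would show if the intervention did nothing and every area's rate stayed constant.

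**Inputs from the article.** Coverage 13.6%, 32.6% and 50.8% in 2014, 2015 and 2016; an aim of 100% by 2018; three years before, two years during.

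**Inputs assumed.** Coverage of 75% in 2017 and 100% during the intervention; areas joined by 2016 have rate 1 and areas joining later have rate *k*. The article gives no value of *k*.

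**Step 1: what extrapolation assumes.** The multiplier is 1/coverage: 1/0.136 = 7.35, 1/0.326 = 3.07 and 1/0.508 = 1.97. Each scales up the covered cases on the premise that the rest of the state looks the same.

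**Step 2: the during-period rate.** 0.508 + 0.492*k*.
- *k* = 0.8: 0.508 + 0.3936 = 0.9016
- *k* = 1.25: 0.508 + 0.615 = 1.123

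**Step 3: the before-period rate.** Calendar-year coverage does not line up with October-to-September years, so two mappings were used.

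(a) *The three before-years take the 2014, 2015 and 2016 coverage.* Only early areas are seen, so the rate is 1. The apparent rate ratio is 0.902 for *k* = 0.8 and 1.123 for *k* = 1.25.

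(b) *They take the 2015, 2016 and assumed 2017 coverage.* The third-year rate is (0.508 + 0.242*k*)/0.75.
- *k* = 0.8: third year 0.7016/0.75 = 0.9355. Mean of annual rates (1 + 1 + 0.9355)/3 = 0.9785; ratio 0.9016/0.9785 = 0.921. Pooled rate (0.326 + 0.508 + 0.7016)/(0.326 + 0.508 + 0.75) = 1.5356/1.584 = 0.9694; ratio 0.930.
- *k* = 1.25: third year 0.8105/0.75 = 1.0807. Mean of annual rates 1.0269; ratio 1.123/1.0269 = 1.094. Pooled rate 1.6445/1.584 = 1.0382; ratio 1.082.

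**Step 4: the range over *k*.** Apparent rate ratio with no true effect, across both mappings and both ways of averaging:

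| *k* (late vs early areas) | Apparent rate ratio |
|---|---|
| 0.7 | 0.85–0.89 |
| 0.8 | 0.90–0.93 |
| 0.9 | 0.95–0.97 |
| 1.0 | 1.00 |
| 1.1 | 1.03–1.05 |
| 1.25 | 1.08–1.12 |
| 1.4 | 1.13–1.20 |

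**Step 5: other patterns.**
- If only the 2014 joiners differ from all later areas, 0.8 gives 0.91–0.97 and 1.25 gives 1.03–1.10.
- If coverage stays at 50.8% in 2017 and reaches only 75% during the intervention, 0.8 gives 0.9355/1, about 0.94, and 1.25 gives 1.08.

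**Step 6: with the composition held fixed.** If the same areas are compared in both periods, or area is adjusted for, the ratio under these assumptions is 1.00 whatever the value of *k*.

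**The case against.** **The method is left open.** The article is condensed, and saying that the catchment must be taken into account leaves room for stratification or a constant-centre check in an analysis plan not shown. This stands in part: such a step may exist. But the article does fix extrapolated rates, all reported cases and an uncontrolled period contrast, and extrapolation, the only technique it names, does not address composition.

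**The limitation is disclosed and other sources exist.** The Discussion concedes the changing coverage. The hospital discharge study examines invasive pneumococcal disease with nearly complete inpatient data against the 15 other federal states. This limits the consequences, because the inference does not rest on the registry alone. It does not repair the registry contrast.

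**Stronger readings that the article does not support.**
- A reader might infer that a false effect will appear. It appears only if early and late areas differ, and it can go in either direction.
- A reader might infer a spurious fall of up to a quarter. That needs early areas at twice the rate of the rest, a before-period frozen at areas covered by 2016, and 100% coverage afterwards: (0.508 × 2 + 0.492)/2 = 0.754. Nothing in the article supports a twofold difference, and full coverage is only an aim.
- A reader might infer that the distortion exceeds any plausible campaign effect. The article gives no expected effect on bacteraemia to compare it with.
- A reader might infer from "will not increase further or will be reduced during the intervention period compared with the baseline measurement before intervention" that any flat, imprecise result would count as success. The article attaches no decision rule to that wording.

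**Conclusion.** The concern holds in conditional form. Followed as written, the registry comparison is biased if early- and late-joining areas differ in incidence or ascertainment, and nothing in the article removes that bias. For a difference of 0.8 to 1.25 between late and early areas, the apparent rate ratio with no true effect runs from about 0.90 to 1.12. These figures rest on the assumed area difference, the assumed 2017 and during-period coverage, and rates constant over time within areas. They show sensitivity and do not estimate the actual bias. Since the result is one of five sources for the secondary outcomes, the point is worth correcting but does not threaten the trial's main conclusions.

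**What to change.** Base the before/during comparison on a Poisson or negative binomial model of case counts by area or centre and year, with the covered population aged 60 or over as offset, area or centre effects, and a term for the intervention period. Report the rate ratio with its 95% confidence interval. Only change within an area then informs the contrast. Keep the extrapolated state-wide rate as a descriptive figure.

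Add two sensitivity analyses:
- a constant-catchment comparison, for example areas covered by 2016, each compared with itself from its joining date;
- a model with a pre-intervention trend term. With only three before-years, and fewer in many areas, this is too fragile to be the main analysis.

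**Cost.** Analysis wording and work, plus precision. Areas joining after 1 October 2017 add nothing to a within-area contrast, and the set covered since 2014 is only about 13.6% of the state, so intervals will be wider. Counts and denominators are needed by area or centre; the article does not say that they are held at that level, so this should be confirmed. At submission, evaluations from sources other than the surveys were still pending, so the change could be fixed before the intervention-period registry results are examined.
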